## Abstract

**Background:**

Robotic-arm-assisted knee arthroplasty allows for more accurate component positioning and alignment and is associated with better patient-reported outcomes compared to manually performed jig-based knee arthroplasty. However, what is not known is whether the addition of an intra-articular sensor (Verasense^TM^) to aid intraoperative balancing of the total knee replacement (TKR) offers improved functional outcomes for the patient. The purpose of this research is to compare the outcomes of patients undergoing a conventional manual knee replacement to those undergoing TKR using robotic-assisted surgery and the Verasense^TM^ to optimise alignment and balance the knee joint, respectively, and assess the associated cost economics of such technology.

**Methods and analysis:**

This randomised controlled trial will include 90 patients with end-stage osteoarthritis of the knee undergoing primary TKR. Patients meeting the inclusion/exclusion criteria that consent to be in the study will be randomised at a ratio of 1:1 to either manual TKR (standard of care) or robotic-arm-assisted TKR with Verasense^TM^ to aid balancing of the knee. The primary objective will be functional improvement at 6 months following surgery between the two groups. The secondary objectives are to compare changes in knee-specific function, joint awareness, patient expectation and fulfilment, satisfaction, pain, stiffness and functional ability, health-related quality of life, cost-effectiveness, and gait patterns between the two groups. Ethical approval was obtained by the Tyne & Wear South Research Ethics Committee, UK. The study is sponsored by the Newcastle Hospitals NHS Foundation Trust.

**Discussion:**

This study will assess whether the improved accuracy of component positioning using the robotic-arm-assisted surgery and the Verasense^TM^ to aid balancing of the TKR offers improved outcome relative to standard manual jig-based systems that are currently the standard of care. This will be assessed primarily according to knee-specific function, but several other measures will also be assessed including whether these are cost-effective interventions.

**Trial registration:**

International Standard Randomised Controlled Trial Number ISRCTN47889316 10.1186/ISRCTN47889316. Registered on 25 November 2019

**Date and version for protocol:**

ROAM Protocol V1.0 (13-12-2018)

**Supplementary Information:**

The online version contains supplementary material available at 10.1186/s13063-021-05936-9.

## Background

Osteoarthritis (OA) of the knee is a degenerative disease and the prevalence increases with age [1]. Total knee replacement (TKR) is a cost-effective intervention for the management of end-stage OA of the knee with improvement in function and pain relief for the patient [2]. The rate of TKR continues to increase year on year in the UK which is thought to be due to growing elderly population that have increasing functional demands [3]. However, it is recognised that between 10 and 20% of patients after TKR are not satisfied with the outcome of their knee after surgery [4]. This results in a proportion of patients undergoing early (before 5 years) revision surgery for which most are due to component malalignment and instability [5]. Recent advances in technology has enabled robotic-assisted surgery to align the TKR within ± 1° with protection of the periarticular soft tissues and intra-operative pressure sensors (Verasense^TM^, OrthoSensor Inc. Dania Beach, FL, USA) can be used to objectively balance the TKR [6–8].

Robotic-assisted knee surgery has evolved over the last decade with increasing evidence of improved component alignment and patient outcomes when compared to manually performed knee surgery [9]. The most commonly used robotic-assisted TKR is the MAKO system. This requires a pre-operative CT scan of the patient’s hip, knee and ankle, which enables the computer navigation to accurately align the component using intra-operative trackers and mapping of the articular surface. The bone cuts, according to the pre-operative plan, are then made using the robotic-arm-assisted saw which also protects the soft tissue structures around the knee (haptic boundary). Non-randomised comparative cohort studies have shown a significant shorter hospital stay, improved early range of movement and function, and a greater rate of satisfaction with the robotic-arm-assisted TKR when compared to manual TKR [10, 11]. Despite the accuracy of the bone cuts to align the knee prosthesis correctly, the soft tissues, which can be scared and tight from the deformity, often need to be released to balance the knee as part of a measured resection technique [12, 13].

The majority of TKR are performed manually by the surgeon using jig-based systems and the knee is balanced by the ‘feel’ though a range of movement. It is recognised that manually performed TKR are misaligned in up to 30% of patients and during the saw cuts soft tissues around the knee may be damaged [14], which can disrupt the balance of the knee. In addition, the definition of a balanced TKR is variable and is dependent upon the surgeons ‘feel’ and hence is not a consistent measurable variable [15]. The Verasense^TM^ (OrthoSensor Inc. Dania Beach, FL, USA) enables the surgeon to objectively balance the TKR through soft tissue releases intra-operatively according to pressure readings within the knee, which has been shown to significantly improve the rate of patient satisfaction [8, 16].

The robotic-arm-assisted TKR has been demonstrated to be 100% accurate in achieving the planned alignment of the knee prosthesis [17], and the Verasense^TM^ (OrthoSensor Inc. Dania Beach, FL, USA) enables the surgeon to objectively balance the TKR with release of the peri-articular soft tissues or further bone cuts [8, 16]. It is hypothesised that robotic-assisted TKR will optimally align the prosthesis and the Verasense^TM^ (OrthoSensor Inc. Dania Beach, FL, USA) will balance the knee with releases of the peri-articular soft tissues which will result in an improved patient outcome when compared to conventional manual TKR.

Two potential reasons for patient dissatisfaction and poor functional outcome after TKR may be due to malalignment of the knee prosthesis and instability (not balanced) of the knee joint [4]. Robotic-assisted TKR offers accurate alignment of the prosthesis and the Verasense^TM^ (OrthoSensor Inc. Dania Beach, FL, USA) enables the surgeon to objectively balance the knee. Whether this improves the outcome of TKR is not known. Therefore, the purpose of this research is to compare the outcomes of patients undergoing a conventional manual knee replacement to those undergoing TKR using robotic-arm-assisted surgery and the Verasense^TM^ (OrthoSensor Inc. Dania Beach, FL, USA) to optimise alignment and balance the knee joint, respectively, and assess the associated cost economics of such technology in the National Health Service in the UK. The null hypothesis is that an optimally aligned and balanced TKR carried out with robotic-assisted surgery and the use of the Verasense^TM^ (OrthoSensor Inc. Dania Beach, FL, USA) does not improve early patient outcomes when compared to a TKR carried out manually using a jig-based system.

## Methods/design

### Objectives

The primary aim is to compare change in functional ability (measured by the functional component of the Western Ontario and McMaster Universities Osteoarthritis Index (WOMAC) [18]) from baseline to 6 months (early) following TKR between the two groups. The secondary outcomes are:
To compare changes in knee function in activities of daily living (measured by the Oxford knee score (OKS) [19]) from baseline to 3, 6 and 12 monthsTo compare changes in joint awareness (measured by the Forgotten Joint Score (FJS) [20]) from baseline to 3, 6 and 12 monthsPre-operative patient expectation and fulfilment at 6 and 12 months will be assessed using the Hospital for Special Surgery Knee Replacement Expectations Questionnaire (HSS) [21, 22]To compare satisfaction using a validated outcome measure at 3, 6 and 12 months [23]To compare pain, stiffness and functional ability (measured by the WOMAC [18]) at 3, 6 and 12 monthsTo compare the health related quality of life using the Euro Qol five dimensional (EQ5D-3L) [24] at baseline and 3, 6 and 12 monthsTo compare the cost effectiveness of the two interventions from a UK NHS perspectiveTo analyse any differences in gait patterns between the two groups

### Trial design

A single site, prospective, parallel randomised controlled superiority trial will be conducted to compare the effectiveness of robotic-arm-assisted and sensor-assisted TKR to standard manual TKR. Participants will be randomly allocated 1:1 to either standard care or the intervention group. Participants randomised to standard care will undergo a conventional manual TKR. Participants randomised to the intervention group will undergo a TKR with the assistance of the MAKO robot and the use of sensors to optimise the balance and alignment of the TKR. Participants will be followed up at routine clinic appointments at 3 and 12 months post op with an additional postal questionnaire at 6 months post op (see flow chart of research activity below). After the 12-month follow-up, the participants will continue with the institution’s standard post-operative care. Screening, enrolment and assessments are illustrated in Figs. 1 and 2 and Additional file 1.

**Fig. 1 Fig1:**
[figure not shown]
Flow diagram illustrating the patient screening, enrolment, randomisation and outcome assessment for the study cohort

**Fig. 2 Fig2:**
[figure not shown]
Schedule of enrolment and outcome assessments

### Eligibility criteria

Participants listed for routine primary TKR for osteoarthritis under the care of the two participating surgeons at the institution will be screened for inclusion. The inclusion criteria are as follows: planned to undergo a primary TKR for end-stage osteoarthritis under the care of the two participating surgeons, age 45–85 at the time of listing for surgery, and suitable candidate for a cruciate retaining TKR (Triathlon prosthesis). The exclusion criteria are as follows: varus deformity of > 20° observed by consultant on examination, patient is unable to comply with the study protocol (incl. refusal for CT scan), female participants who is pregnant, lactating or planning pregnancy during the course of the study, requires patella resurfacing, inability to understand the patient information for the study, provide written informed consent or answer study questionnaires for cognitive or language reasons, or any other significant disease or disorder which, in the opinion of the Investigator, may either put the participants at risk because of participation in the study or influence the result of the study, or the participant’s ability to participate in the study.

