### Recruitment

Patients listed for a routine primary TKR under the care of the participating surgeons will be screened by the treating clinician. A screening form will be completed to confirm name, age, hospital number, listed for routine primary TKR, suitable candidate for a cruciate retaining TKR (Triathlon prosthesis), no varus deformity of > 20°, capacity to provide informed consent and no pre-existing condition that limits function and potential outcome of surgery. After making the initial approach, the consultant will request the patient’s permission to be approached by the research team who will provide the patient information sheet, discuss the study in more detail and confirm eligibility. Patients will be encouraged to take the study information and discuss with their family and friends before making a decision to participate. The research team will reconfirm the eligibility criteria below and record that: the patient is able to comply with the study protocol (incl. refusal for CT scan) and that female participants are not pregnant, lactating or planning pregnancy during the course of the study.

Eligible patients are identified by the treating consultant surgeon and listed for surgery and a screening form is completed but are not approached at that time will be sent a letter of approach from the consultant along with the patient information sheet. The research team will then contact the patient to discuss the study in more detail and answer any questions. All eligible patients who agree to participate in the study will be invited to attend a research clinic to provide written informed consent and complete baseline assessments before randomisation.

Participants will be asked to attend a research appointment to provide written informed consent and complete a CRF and a number of pre-operative questionnaires recording their knee function, expectations and general health. Participants will be asked to carry out a gait assessment which involves walking over an instrumented walkway (Tekscan instrumented mat system, Tekscan Inc. Boston, USA) that is 3 m long plus 1 m either side, six times and standing still on an individual instrumented mat of the walkway for 1 min. After completing the baseline assessments participants will be randomised to one of two groups. Patients will be informed of their allocation and the research staff will reinforce the treatment allocation and arrange a CT for those randomised to the intervention group.

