### Defined end of trial

The end of trial is the date of the 12-month follow-up visit of the last participant. Each participant has the right to withdraw from the study at any time. In addition, the investigator may discontinue a participant from the study at any time if the investigator considers it necessary for any reason including ineligibility (either arising during the study or retrospective having been overlooked at screening); significant protocol deviation, i.e. intervention not used as intended at time of surgery; significant non-compliance with treatment regimen or study requirements; an adverse event which requires discontinuation of the study medication or results in inability to continue to comply with study procedures; consent withdrawn; or lost to follow-up.

Participants who wish to withdraw consent for the trial or whose participation from the trial is discontinued will have anonymised data collected up to the point of that withdrawal of consent included in the analyses unless the participant specifically asks for all data collected to be destroyed. No additional data will be collected from the participant. The reason for withdrawal will be recorded in the CRF. Participants who withdraw once they have been randomised will not be replaced. If the participant is withdrawn due to an adverse event, the investigator will arrange for follow-up visits or telephone calls until the adverse event has resolved or stabilised.

At the end of the trial, patient will resume standard practice of care of the study centre in place at that time for follow-up of routine TKR.

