The intervention group (undergoing robotic-arm-assisted surgery) will require a pre-operative CT scan as part of the planning process for robotic-assisted surgery. The information from the CT scan will be used to create a 3D model of the patient’s bony anatomy to plan the positioning and sizing of the implant. The research team will make every effort to coordinate the CT scan with the patient’s routine pre-assessment clinic to limit the requirement for additional hospital visits. The CT scan will be anonymised using a dedicated study code and transferred to Stryker using an encrypted data drop box. The CT scan will be reconfigured and transferred back using an encrypted data drop box. This data will be used by the MAKO technician to plan the individuals’ surgery. The participants will receive the same Triathlon TKR with a highly crossed linked (X3) cruciate retaining polyethylene insert and the same surgical approach to the knee joint will be employed. Instead of using a manual jig-based system and a handheld saw to prepare the bone surfaces for the implant, the MAKO robotic-arm will be used by the surgeon to cut the bone at the required alignment. The MAKO is a robotic arm that the surgeon guides to cut the diseased bone instead of using a manual jig and the handheld saw. The information from the CT scan will be used to create a 3D model of the patient’s bony anatomy and will used to plan the positioning of the implant. During the operation, trackers (markers for the robot to assess where the knee is in space) will be positioned on the tibia and femur using two treaded pins (4mm) through a small incision (2cm) a hands width above and below the joint. Once the trackers are in place, registration of the knee joint surface is performed. The specified bone cuts are then performed using the robotic arm. The specified bone cuts will be 5° of valgus and neutral flexion/extension for the femoral component and zero varus/valgus with 3° of posterior slope for the tibial component relative to the mechanical axis. When the implant is in place, the Verasense^TM^ (OrthoSensor Inc. Dania Beach, FL, USA) will then be inserted into the knee joint. Pressures in the medial and lateral compartments will be recorded throughout a range of movement (extension to flexion). Soft tissue releases will be performed as required to balance the knee, defined as a pressure difference of less than 15Ibs in medial and lateral compartments, throughout a range of motion [16].

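### The patella-resurfacing exclusion has no stated time of assessment, and the discontinuation rule lets a patient in whom the need emerges after allocation be removed with loss of the 6-month WOMAC

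*Protocol article*

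**What the plan says.** - **Eligibility criteria.** One exclusion reads "requires patella resurfacing, inability to understand the patient information for the study" (the second half begins the next criterion). No assessor or occasion is attached to the patella item. Some neighbouring criteria have one: "varus deformity of > 20° observed by consultant on examination" and "age 45–85 at the time of listing for surgery". Patella resurfacing is not mentioned again in the article.
- **Recruitment.** The screening form's items end with "no varus deformity of > 20°, capacity to provide informed consent and no pre-existing condition that limits function and potential outcome of surgery". A second check begins "The research team will reconfirm the eligibility criteria below and record that: the patient is able to comply with the study protocol" and adds pregnancy, lactation and planned pregnancy. Neither list names the patella. The section also says that the research team will "discuss the study in more detail and confirm eligibility", and that eligible patients who agree are consented and assessed at baseline before randomisation.
- **Allocation.** Randomisation follows consent and baseline data. Patients and clinicians know the arm; staff doing follow-up assessments and the analysts do not.
- **Defined end of trial.** The investigator may discontinue a participant for, among other grounds, "ineligibility (either arising during the study or retrospective having been overlooked at screening", or for a significant protocol deviation. Data up to that point are kept unless the participant asks for them to be destroyed, and nothing further is collected. Participants who withdraw after randomisation are not replaced.

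**The concern.** An eligibility criterion should be settled before allocation. If it can be applied afterwards by someone who knows the arm, membership of the analysed group may depend on the arm, and randomisation no longer protects the comparison. Here the criterion has no fixed time, and the discontinuation rule accepts ineligibility that arises during the study. That rule also ends data collection, so a patient removed at or around surgery has no 6-month WOMAC function score. At stake are a possible selective loss of primary outcomes and some loss of power in a trial with almost no spare patients.

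**Working it through.** **1. Is the removal route open on the text?**

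| Step | Where | What it fixes |
|---|---|---|
| Criterion | Eligibility criteria | Need for resurfacing excludes; no time or assessor |
| Checks | Recruitment | Two itemised lists without it; a general confirmation of eligibility |
| Allocation | Allocation | After consent and baseline; clinicians know the arm |
| Removal | Defined end of trial | Investigator may discontinue for ineligibility found later or for protocol deviation |
| Data | Defined end of trial | None collected after discontinuation |

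Read together, the sections allow removal after allocation with loss of the primary outcome. They do not say that it will happen or how often.

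**2. The plan's own sample size.** Inputs from Sample size: difference 15, SD 26.5, one-sided alpha 0.05, power 80%, 10% loss.

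- n per arm = 2 × (1.645 + 0.842)² × 26.5² / 15² = 2 × 6.18 × 3.121 ≈ 38.6, so 39 per arm or 78 in total. The plan states 80.
- 80 / 0.90 = 88.9, so 89. The plan randomises 90.
- Expected evaluable: 90 × 0.90 = 81, one more than the 80 required.

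The plan's figures are reproduced to within two patients.

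**3. Power if further patients are removed.** The removal rate x is assumed; the article gives none. With m = 45 × 0.90 × (1 − x) per arm, power ≈ Φ[15 / (26.5 × √(2/m)) − 1.645].

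| x (assumed) | Evaluable | m per arm | Power, normal approximation | Power, noncentral t |
|---|---|---|---|---|
| 0 | 81 | 40.5 | 81.7% | 81.1% |
| 5% | 77 | about 38.5 | 79.9% | 79.3% |
| 10% | 73 | about 36.5 | 78.0% | 77.3% |

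The loss is about 2 points at 5% and just under 4 points at 10% by either method. This supposes that every such patient is discontinued.

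**4. Bias if removal is from one arm only.** If a fraction f of an arm is removed and its mean change differs by d points from the patients who remain, the arm mean shifts by f × d. Both inputs are assumed.

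- f = 0.05, d = 10: 0.5 points.
- f = 0.10, d = 20: 2.0 points.

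With counts, if k of 45 are removed and their mean lies g points from the original arm mean, the shift is k × g / (45 − k).

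- k = 3, g = 20: 60 / 42 = 1.4 points.
- k = 1, g = 10: 10 / 44 = 0.2 points.

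All of these are small against 15 points.

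**The case against.** **The article already puts eligibility before randomisation.** Patients are screened against the criteria, eligibility is confirmed, and only then are they consented and randomised. Several other criteria also lack a time point, and an exclusion without one is naturally read as judged at screening. This stands as the likely intention. It does not settle what happens when the need becomes apparent later, which the discontinuation rule expressly provides for.

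**The screening form itself is not shown.** A condensed article may summarise it, and a missing line in a summary is no defect in the form. This stands, so the missing item is context only. For the same reason nothing is made of the form's wording on pre-existing conditions. A reader might infer that the form admits a narrower population than the eligibility criteria. It may simply paraphrase their clause on significant disease, and a narrower population is not shown.

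**A reader might infer an arm-dependent trigger.** Only the intervention group "will require a pre-operative CT scan as part of the planning process for robotic-assisted surgery", so the CT might seem to prompt findings of ineligibility in one arm. The article does not support that. It gives the CT's purpose as implant positioning, sizing and bone cuts, and never links it to the patella or to a second look at eligibility. Nor does it say that the need is judged in theatre, or that the discontinuing investigator is the operating surgeon.

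**The real source is the general discontinuation rule.** That rule covers every criterion and is permissive, so a late finding does not force removal. This is largely right, and it is why the main change belongs there. An analysis plan may already require analysis as randomised, but it cannot recover a 6-month score that the protocol stops collecting.

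**Conclusion.** The point holds in a limited form. The criterion has no stated time of assessment. If the need for resurfacing emerges after allocation, the stated discontinuation rule permits removal by an investigator who may know the arm, and the 6-month WOMAC is then lost. The documents do not show that this will be frequent, that it will differ between arms, or that eligibility goes unchecked before randomisation.

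On assumed rates of 5% to 10%, power falls by about 2 to 4 percentage points. Under the one-arm scenarios above, an arm mean shifts by roughly 0.2 to 2 points against a target of 15. These sizes rest wholly on assumed rates, assumed differences and discontinuation of every affected patient. The case for change is that the rule permits removal with knowledge of the arm and can be closed cheaply; no large error has been found.

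**What to change.** 1. In Eligibility criteria, state that the need for patella resurfacing is assessed once, by the surgeon, before randomisation.
2. In Defined end of trial, state that a need identified after allocation is recorded by arm as a deviation and is not a ground for ending follow-up, whether as ineligibility or as protocol deviation. The patient is followed to 12 months, subject to consent, and analysed in the randomised group.

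This concerns follow-up and analysis only and proposes no clinical rule on when a patella is resurfaced.

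The cost is one or two sentences in an amendment. The downside is that a few resurfaced knees stay in the analysis and may add slight variability. Trial status gives May 2021 as the estimated end of recruitment and December 2022 as the estimated end of follow-up. If recruitment has closed, the first change has no effect. The second still helps while follow-up is open, and reporting by arm helps until analysis is complete.
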